#### **1. TRIAL DESIGN:**

This is a randomized controlled trial of the early introduction of allergenic foods (and other foods) from three months of age in the general population with target accrual of 1302 participants. Mothers were recruited initially antenatally from two large antenatal units (Kingston and St Thomas' Hospitals) (antenatal recruitment ceased November 2009) and subsequently postnatally using invitations mailed to parents who are members of the Bounty Parenting Club.

All infants will be followed up until three years of age by which point the impact of the intervention on the primary outcome (food allergy) and secondary outcomes - asthma (including atopic wheeze), eczema, allergic rhinitis (including aero-allergen sensitization), combined food allergy prevalence (including food sensitization) and the prevalence of combined allergic disease will be known. As described in the EAT Protocol, Figure 5, Overall Study Design

#### **2. TRIAL OBJECTIVES:**

To determine whether early introduction of allergenic foods (from three months of age) reduces the prevalence of food allergy (FA), eczema, asthma and allergic rhinitis (AR) by three years of age. This study will provide an informed basis for future infant feeding practices in both atopic and normal infants.

#### **3. TRIAL ARMS**

**3.1 Early introduction group:** Dietetic controlled introduction of allergenic foods from three months of age. A pureed fruit / vegetable or baby rice mixed with breast milk or water commenced first, followed by cow's milk based yoghurt. Subsequently egg, sesame, fish, and peanut introduced in a randomized order, with wheat introduced last. (For further details on ingestion timing and quantities for each food, see protocol).

**3.2 Standard introduction group:** Standard introduction following current UK Government infant feeding advice (exclusive breastfeeding until around 26 weeks of age) and avoid introducing foods that may cause allergies before six months of age (cow's milk, egg, wheat, peanuts, tree nuts, seeds, fish and shell fish).

#### **4.0 SAMPLE SIZE AND POWER**

The trial has 80% power to detect a 50% relative reduction in the absolute prevalence (from 8% in the standard introduction arm to 4% in the intervention arm) of food allergy by three years of age, assuming a 15%

drop out rate. These numbers were used to calculate the final cohort size of 1302 infants (651 infants in each arm) yielding a final cohort size of 1106 infants (553 infants in each arm) after drop out (based on the amended protocol September 2010). The whole cohort is to be followed up until the primary assessment point at three years of age.

The study is also designed so that it has sufficient power to detect a protective effect in the high risk sub-population. The high risk children are defined as being the 25% with eczema present at three months of age, who have an estimated prevalence of food allergy of 30%. It is estimated that with 15% loss to follow up, there will be 276 high risk children completing the study, 138 in each group. The study has 99% power to detect a reduction from 30% to 10% amongst the high risk participants in the intervention group and 85% to detect a reduction from 30% to 15%. See protocol (Protocol section 9.3: Contract variation September 2010). The study is not powered to detect a reduction in allergy to individual foods.

## **5. LOSS TO FOLLOW UP**

1302 infants will be recruited into the study at three months of age. A drop out figure of 15% has been estimated based on the low rate observed in the LEAP study and in the EAT study at the time of the revised protocol. (Protocol change September 2010).

## **6. RANDOMIZATION AND BLINDING**

Participants are randomly assigned to treatment using a centrally administered randomization service (ALEA). The randomization is not stratified given the number of participants. Given the nature of the intervention, the study participants cannot be blinded to their allocation group. However, the study outcomes are based on food challenges that include double-blinded assessment and objective measures of sensitization (skin prick test results) and specific IgE measurements. The latter are measured by laboratory staff blinded to the child's allocation status.

## **7. ENDPOINTS**

### **7.1 Primary Endpoint**

The period prevalence of IgE mediated food allergy to the six intervention foods between one and three years of age in both arms.

### **7.2 Secondary Endpoints**

#### **7.2.1 Period (one to three years of age) prevalence food outcomes**

1. The period prevalence of all IgE mediated food allergy between one and three years of age in both arms.
2. The period prevalence of all reported food allergy (IgE and non-IgE mediated) between one and three years of age in both arms.
3. The period prevalence of sensitization to food between one and three years of age in both arms. (Defined in Protocol, Section 3.9).
4. The total number of foods (of the six intervention foods) to which IgE mediated food allergy has been diagnosed between one and three years of age in both arms amongst children with IgE mediated allergy to one or more of the six intervention foods.
5. The total number of foods (any foods) to which IgE mediated food allergy has been diagnosed between one and three years of age in both arms amongst children with IgE mediated allergy to one or more foods.

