#### **7.2.2 Cumulative (by three years of age) prevalence food outcomes**

1. The cumulative prevalence of IgE mediated food allergy to the six intervention foods by three years of age.
2. The cumulative prevalence of all IgE mediated food allergy by three years of age.
3. The cumulative prevalence of all food allergy (IgE and non-IgE mediated) by three years of age.
4. The cumulative prevalence of non-IgE mediated food allergy by three years of age.
5. The cumulative prevalence of sensitization (defined in Section 3.9) to the six foods by three years of age.
6. The total number of foods (of the six intervention foods) to which IgE mediated food allergy has been diagnosed by three years of age amongst children with IgE mediated allergy to one or more of the six intervention foods.
7. The total number of foods (any foods) to which IgE mediated food allergy has been diagnosed by three years of age amongst children with IgE mediated allergy to one or more foods.

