### **7. STATISTICAL ANALYSIS**

#### **8.1.1 Intention to Treat Analysis**

These will be the main analyses and the ones that are used to quantify the efficacy of the intervention. Only ITT results will be reported in the abstracts of the main publication and trial report.

All children allocated to each of the two study arms will be analysed together as representing that treatment arm, whether or not they received or completed the prescribed regimen. This will be done after the three year assessment for the period prevalence of IgE mediated food allergy to the six intervention foods between one and three years of age in both arms.

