### **8.3 ANALYSIS OF ENDPOINTS ITT**

#### **8.3.1 Analysis of Primary Endpoint TABLE 2**

The main analysis will compare the period prevalence of IgE mediated food allergy to the six intervention foods between one and three years of age in both arms (protocol, Section 3.3.1). Table 1 will also include allergy to each of the six constituent foods by treatment group. The outcomes to be analysed by intervention group, are listed below:

1. Period prevalence of IgE mediated food allergy to one or more of the six intervention foods between one and three years
2. Period prevalence of IgE mediated food allergy to each of the six intervention foods between one and three years:
  - i. Cow's milk
  - ii. Egg
  - iii. Fish

- iv. Wheat
- v. Peanut
- vi. sesame

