**TABLE 3: Period and cumulative prevalence (one to three years of age) food outcomes as listed below:**

1. The period prevalence of all IgE mediated food allergy between one and three years of age in both arms.
2. The period prevalence of all reported food allergy (IgE and non-IgE mediated) between one and three years of age in both arms.
3. The period prevalence of sensitization to food between one and three years of age in both arms (defined in Protocol, Section 3.9).
4. The total number of foods (of the six intervention foods) to which IgE mediated food allergy has been diagnosed between one and three years of age in both arms amongst children with IgE mediated allergy to one or more of the six intervention foods.
5. The total number of foods (any foods) to which IgE mediated food allergy has been diagnosed between one and three years of age in both arms amongst children with IgE mediated allergy to one or more foods.
6. The cumulative prevalence of IgE mediated food allergy to the six intervention foods by three years of age.
7. The cumulative prevalence of all IgE mediated food allergy by three years of age.
8. The cumulative prevalence of all food allergy (IgE and non-IgE mediated) by three years of age.
9. The cumulative prevalence of non-IgE mediated food allergy by three years of age.
10. The cumulative prevalence of sensitization (defined in Section 3.9) to the six foods by three years of age.
11. The total number of foods (of the six intervention foods) to which IgE mediated food allergy has been diagnosed by three years of age amongst children with IgE mediated allergy to one or more of the six intervention foods.
12. The total number of foods (any foods) to which IgE mediated food allergy has been diagnosed by three years of age amongst children with IgE mediated allergy to one or more foods.

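### Four secondary endpoints compare the number of food allergies only among children who became allergic, so the contrast is not intention to treat and its sign cannot be read as a treatment effect

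*SAP*

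**What the plan says.** Four secondary endpoints concern the number of foods to which a child has IgE mediated allergy, and each is restricted to children who have such an allergy:

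- Section 7.2.1 item 4 (period, six foods): "in both arms amongst children with IgE mediated allergy to one or more of the six intervention foods".
- Section 7.2.1 item 5 (period, any food): "in both arms amongst children with IgE mediated allergy to one or more foods".
- Section 7.2.2 item 6 (cumulative, six foods), repeated in Table 3: "by three years of age amongst children with IgE mediated allergy to one or more of the six intervention foods".
- Section 7.2.2 item 7 (cumulative, any food): "by three years of age amongst children with IgE mediated allergy to one or more foods".

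Table 3 carries them as items 4, 5, 11 and 12. It belongs to section 8.3.2, which presents secondary endpoints by intervention group within section 8.3, headed "ANALYSIS OF ENDPOINTS ITT". Section 8.1.1 defines that approach: "All children allocated to each of the two study arms will be analysed together as representing that treatment arm". Section 8.1.3 applies two-sided 5% testing to all analyses, and nothing marks these four as descriptive.

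The primary endpoint in section 7.1 is "The period prevalence of IgE mediated food allergy to the six intervention foods between one and three years of age in both arms". Section 4.0 powers the trial for a fall "from 8% in the standard introduction arm to 4% in the intervention arm".

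**The concern.** Randomisation makes the arms comparable as a whole. It does not make the children who later become allergic comparable, because the intervention is intended to change which children those are. For 7.2.1 item 4 the selecting event is the primary endpoint itself. The other three endpoints select on any-food or cumulative allergy, which are closely related outcomes but not the primary endpoint.

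A difference between arms in foods per allergic child therefore mixes two things: an effect on the number of foods, and a change in who is counted. If early introduction mainly prevents single-food allergy, the cases that remain are weighted towards multi-food children. Their average rises although no child is worse off and the total burden is lower. If it mainly prevents multi-food allergy, the average falls. The table cannot tell a reader which of these has happened. Published as ITT evidence on infant feeding, a higher figure in the early introduction arm could be read as harm.

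**Working it through.** **Inputs from SAP section 4.0:** 8% versus 4%, 80% power, 553 completers per arm, 651 recruited per arm, 15% drop-out. Two-sided 5% is from section 8.1.3.

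**The plan's own figure.** The two-proportion formula with pooled variance and no continuity correction gives 553 per arm (power at 553 is 80.06%). Inflating for drop-out, 553 / 0.85 = 651. Both stated figures reproduce.

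**Children entering 7.2.1 item 4.** 553 × 0.08 = 44.2 and 553 × 0.04 = 22.1, so about 44 versus 22, or 66 of 1106 completers. The SAP gives no rates for the any-food or cumulative versions, so this figure applies to item 4 only.

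**Assumptions for the illustration.** The SAP gives no distribution of foods per allergic child and names no summary for these counts. I read the endpoint as a mean per allergic child. Of the 44 control cases, 70% (30.8) have one food and 30% (13.2) have three. The intervention prevents 22 cases and makes no child worse. Let *f* be the share of prevented cases that are single-food.

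- Control total = 30.8 × 1 + 13.2 × 3 = 70.4; mean per allergic child = 70.4 / 44 = 1.60.
- Early-arm total = 70.4 − 22*f* − 3 × 22(1 − *f*); mean per allergic child = that total / 22.
- Fall in total = 1 − early-arm total / 70.4.

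At *f* = 1 the early-arm total is 70.4 − 22 = 48.4, the mean is 48.4 / 22 = 2.20, and the fall is 1 − 48.4 / 70.4 = 31%. At *f* = 0.5 the total is 70.4 − 11 − 33 = 26.4, the mean is 1.20, and the fall is 63%. The last column comes from simulated trials with a two-sample z test on the allergic children.

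| *f* | Mean foods per allergic child, control vs early | Fall in total allergies | Significant harm shown |
|---|---|---|---|
| 100% | 1.60 vs 2.20 | 31% | about 64% |
| 90% | 1.60 vs 2.00 | 38% | about 34% |
| 80% | 1.60 vs 1.80 | 44% | about 12% |
| 70% | 1.60 vs 1.60 | 50% | about 2% |
| 50% | 1.60 vs 1.20 | 63% | 0% (about 57% show significant benefit) |

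At 70%, prevention is unrelated to the number of foods and the harm rate is simply the nominal one-tail rate. Replacing three foods by two gives nearly the same test results.

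**A different mechanism.** If every child's risk for each food is lowered by the same amount on the logit scale, with a shared susceptibility across foods, the mean per allergic child falls, for example from 1.37 to 1.24. The direction depends on facts that the SAP does not supply.

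**All-children count.** The mean over 553 completers, with 0 for no allergy, moves with the total and so falls in every row. At *f* = 100% it goes from 70.4 / 553 = 0.127 to 48.4 / 553 = 0.088. A test on it is significant for benefit in about 27% of trials in that row: modest power, but the right direction on average.

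**The case against.** Several objections have force.

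- **The wording is total number of foods, not mean.** Read as an arm total, the restriction changes nothing, because non-allergic children add zero. That reading is possible. But a phrase confining the endpoint to allergic children would then do no work, so a per-child comparison within that group is the more natural reading. The SAP should settle it.
- **The burden is visible elsewhere.** Table 2 lists period prevalence for each of the six foods by arm over all children, and the sum of those six counts is the total number of six-food allergies. Table 3 also gives overall allergy prevalence. This is a real mitigation for 7.2.1 item 4. It supplies no formal comparison of the count, and no per-food list is specified for the any-food or cumulative versions.
- **These are secondary endpoints.** The primary analysis and the sample size are untouched.

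A reader might infer more than the document supports: that the planned analysis will turn a benefit into apparent harm, or will do so in about two thirds of trials. That figure belongs to the extreme case in which every prevented allergy is single-food, and nothing in the SAP says this is expected. A reader might also infer that all four endpoints condition on the primary outcome; only 7.2.1 item 4 does.

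**Conclusion.** The point stands in a limited form. All four endpoints are by-arm comparisons within groups formed after randomisation by an outcome that the intervention targets. They do not meet the SAP's own definition of ITT in section 8.1.1, although section 8.3 labels them so. This conclusion needs no assumption about the data.

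The size of the distortion does need assumptions: a mean per allergic child, a 70/30 split between one and three foods, and the planned 8% and 4% rates. On these, false significant harm ranges from 0% to about 64% of trials, and at the lower end the comparison favours early introduction instead. Total allergies fall by 31% to 63% throughout. Whichever sign appears, it cannot be interpreted as a treatment effect. This should be fixed, but it does not threaten the trial's main conclusion.

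**What to change.** In sections 7.2.1 and 7.2.2 and in Table 3, define the four counts over all randomised children, with 0 for a child with no allergy, and handle unassessed children under section 8.4. Compare arms by a ratio or difference of mean counts with robust or bootstrap standard errors. A proportional-odds model is a poor default: in the extreme row above the effect is confined to having any allergy, and the number of three-food children is 13.2 in both arms, so the odds are not proportional. The randomisation is unstratified, and the correction does not depend on adjusting for enrolment eczema.

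Keep the distribution of the number of foods among allergic children if it is wanted, labelled as descriptive, outside the ITT comparisons and without a test or p value.

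The cost is SAP wording and slightly more analysis. No new data are needed.

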#### **7.2.2 Cumulative (by three years of age) prevalence food outcomes**

1. The cumulative prevalence of IgE mediated food allergy to the six intervention foods by three years of age.
2. The cumulative prevalence of all IgE mediated food allergy by three years of age.
3. The cumulative prevalence of all food allergy (IgE and non-IgE mediated) by three years of age.
4. The cumulative prevalence of non-IgE mediated food allergy by three years of age.
5. The cumulative prevalence of sensitization (defined in Section 3.9) to the six foods by three years of age.
6. The total number of foods (of the six intervention foods) to which IgE mediated food allergy has been diagnosed by three years of age amongst children with IgE mediated allergy to one or more of the six intervention foods.
7. The total number of foods (any foods) to which IgE mediated food allergy has been diagnosed by three years of age amongst children with IgE mediated allergy to one or more foods.

### **7.2.3 Point prevalence food outcomes**

1. The point prevalence of IgE mediated food allergy to the intervention foods (excluding sesame and peanut) at the one year assessment.
2. The point prevalence of IgE mediated food allergy to the intervention foods at the three year assessment.

### **7.2.4 Other allergic disease outcomes**

1. The point prevalence of eczema at one year and three years of age and cumulative prevalence of eczema by three years of age.
2. The severity of eczema at one year and three years of age.
3. The prevalence of allergic rhinitis at three years of age.
4. The prevalence of inhalant allergen sensitization at one year and at three years of age by skin prick test.
5. The prevalence of inhalant allergen sensitization at one year and at three years of age by specific IgE measurement.
6. The prevalence of the atopic wheeze phenotype at three years of age.

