### **7.2.5 Composite allergy outcome**

1. The prevalence of combined allergic disease (a composite of cumulative IgE mediated food allergy to all foods, atopic wheeze phenotype, eczema and allergic rhinitis) at three years of age.
2. The prevalence of combined allergic disease (a composite of cumulative IgE and non-IgE mediated food allergy to all foods, atopic wheeze phenotype, eczema and allergic rhinitis) at three years of age.

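### Cumulative eczema by three years, as worded, counts eczema already present at enrolment; this dilutes the relative risk and lowers power to show prevention, so a new-onset analysis should be added

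*SAP*

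**What the plan says.** SAP section 7.2.4, item 1, names point prevalence of eczema at one and three years and the "cumulative prevalence of eczema by three years of age". Section 8.3.2 repeats both for Table 4. Neither place says when the cumulative count starts or how infants with eczema at entry are handled.

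The timing comes from other sections. Section 5: "1302 infants will be recruited into the study at three months of age". Section 3.1 describes the active arm as "Dietetic controlled introduction of allergenic foods from three months of age". Section 4.0 identifies the high-risk group as "the 25% with eczema present at three months of age".

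On analysis, section 8.1.1 compares all allocated children by arm. Section 8.1.3 reports binary outcomes as proportions and relative risks with a chi-square or Fisher test. Enrolment eczema is a baseline variable (section 8.2, item 14). It becomes a covariate only in sensitivity analyses, and only if a clinically important imbalance is seen (section 8.1.3).

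**The concern.** The SAP separates period outcomes, which run from one to three years, from cumulative outcomes, which run up to three years. The plain reading of the cumulative eczema outcome is therefore eczema at any time up to three years, and that includes eczema present at three months. An infant with eczema at entry is already an event before allocation can act.

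Section 2 asks whether early introduction reduces eczema. A block of events that the intervention cannot prevent, equal in expectation in the two arms, pulls the relative risk toward 1 and adds variance. A real effect on new eczema could then look small or fail to reach significance, and be read as absence of prevention.

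**Working it through.** **Inputs from the SAP.** Share with eczema at three months b = 0.25 (section 4.0, a planning estimate). Evaluable infants n = 553 per arm (section 4.0: "yielding a final cohort size of 1106 infants (553 infants in each arm) after drop out"). Two-sided 5% level (section 8.1.3).

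**Assumed inputs, not in the SAP.** q, the standard-arm risk of new eczema after enrolment in infants free of it at enrolment: 10% to 40%. r, the true relative risk for new eczema: 0.5 to 0.8. Dropout is taken as unrelated to enrolment eczema, as in the SAP's own high-risk calculation.

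**Power formula**, with p̄ the mean of p1 and p2:

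power = Φ{ [ |p1 − p2| − 1.96 √(2 p̄(1 − p̄)/n) ] / √[ (p1(1 − p1) + p2(1 − p2))/n ] }

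**Step 1: the plan's own figures.** For 8% against 4% at 80% power the formula gives 553 per arm, and 553/0.85 = 651 recruited per arm. Power at 553 is 80.1%. For the high-risk group with 138 per arm, 30% against 10% gives 98.8% and 30% against 15% gives 85.1%. All agree with section 4.0. The SAP states no power for eczema, so there is no eczema figure to reproduce.

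**Step 2: the cumulative outcome.**

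- Standard arm: b + (1 − b)q
- Early introduction arm: b + (1 − b)qr
- Cumulative relative risk: [b + (1 − b)qr] / [b + (1 − b)q]

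**Step 3: the new-onset outcome.** Risks are q and qr, in 0.75 × 553 ≈ 415 infants per arm.

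**Step 4: one case in full (q = 20%, r = 0.5).**

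- Cumulative: 0.25 + 0.75 × 0.20 = 40.0% against 0.25 + 0.75 × 0.10 = 32.5%. Relative risk 0.325/0.400 = 0.81. Power = Φ[(0.0750 − 0.0567)/0.0288] = 74%.
- New onset: 20% against 10%. Relative risk 0.50. Power = Φ[(0.1000 − 0.0486)/0.0245] = 98%.
- Of the standard-arm cumulative events, 0.25/0.40 = 62.5% were present at enrolment.

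**Step 5: the range.**

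| Onset q | True RR r | Cumulative risks | Cumulative RR | Power, cumulative (553/arm) | Power, new-onset (415/arm) |
|---|---|---|---|---|---|
| 10% | 0.5 | 32.5% v 28.75% | 0.885 | 27% | 78% |
| 10% | 0.67 | 32.5% v 30.0% | 0.92 | 14% | 40% |
| 20% | 0.5 | 40.0% v 32.5% | 0.81 | 74% | 98% |
| 20% | 0.67 | 40.0% v 35.1% | 0.88 | 40% | 72% |
| 30% | 0.67 | 47.5% v 40.1% | 0.84 | 70% | 91% |
| 40% | 0.5 | 55.0% v 40.0% | 0.73 | >99% | >99% |
| 40% | 0.67 | 55.0% v 45.1% | 0.82 | 91% | 98% |
| 40% | 0.8 | 55.0% v 49.0% | 0.89 | 52% | 67% |

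Across the 15 combinations examined (q = 10, 15, 20, 30 and 40%; r = 0.5, 0.67 and 0.8), the cumulative relative risk was always nearer 1. Its power was never higher, despite the larger denominator.

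**Step 6: the risk difference.** It equals (1 − b)q(1 − r). In the worked case this is 0.75 × 10 = 7.5 percentage points, the true effect averaged over all randomised infants. It is not biased.

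**Step 7: would the planned adjustment help?** It is triggered only by imbalance. Even then, every infant with enrolment eczema is an event, so a logistic model cannot give a finite estimate for that covariate.

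**The case against.** The strongest reply has four parts.

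- **Definition.** The SAP leaves some definitions to the protocol, which is not at hand and could give a later start to the count. This stands as a caveat. But the eczema item cites no protocol section, whereas the food-sensitization item in 7.2.1 does.
- **Objective.** Section 2 speaks of prevalence by three years, so an all-infant outcome matches the stated aim. This stands, and it is a reason to keep that outcome. It does not make the outcome a good test of prevention.
- **Other outcomes.** Point prevalence and severity at one and three years are reported alongside and do not automatically count enrolment cases. This is true, but they mix prevention of new eczema with persistence of old eczema.
- **Assumptions.** The onset risks and effects are not the SAP's, and at high onset with a large effect the loss disappears. This stands. The direction is general; the size is not.

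A reader might also infer three stronger things that the document does not support:

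- **That the comparison is biased.** Enrolment cases are balanced in expectation, and the risk difference is unbiased.
- **That a stated power figure is wrong.** Section 4.0 claims power for food allergy only, and its figures reproduce.
- **That the composite in 7.2.5 carries the same fixed events.** It is defined as "a composite of cumulative IgE mediated food allergy to all foods, atopic wheeze phenotype, eczema and allergic rhinitis" and assessed at three years. There the word cumulative attaches to food allergy, so the text does not show that eczema enters cumulatively.

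**Conclusion.** The point holds for one secondary outcome. As worded, cumulative eczema includes cases that predate the intervention. This dilutes the relative risk, which is the effect measure the SAP has chosen, and lowers power to detect prevention of new eczema. Under the assumed 10% to 40% onset, a halving of new eczema shows as a relative risk between about 0.885 and 0.73. The power lost runs from large (27% against 78%) through moderate (52% against 67%) to negligible (40% onset with a halving).

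The direction holds for any enrolment share above zero. The size depends on the 25% planning estimate and on the assumed onset and effect. The conclusion also rests on reading the outcome as eczema at any time up to three years.

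**What to change.** State in section 7.2.4 when the cumulative count begins. Then specify, in 7.2.4 and in Table 4, new-onset eczema between enrolment and three years among infants without eczema at enrolment, and name it as the analysis used to judge eczema prevention. The set is defined by a baseline variable, so the comparison remains randomised.

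Keep the cumulative, point-prevalence and severity outcomes in all infants, and report point prevalence and severity by enrolment eczema status. Replacing the all-infant outcome would be a mistake, because it would drop the high-risk quarter that section 4.0 also had in view.

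The cost is SAP wording and one more secondary analysis, in about three quarters of the infants. No new data are needed, since enrolment eczema is already collected.
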